#### Process evaluation

A separate team of Gram Vikas staff will be trained by the Emory research team to document intervention activities. The staff member will sit-in on the activity and discretely fill-out a survey based on their observations, recording participant engagement and whether each specific activity step was completed. As part of a data quality check, a trained Emory research assistant (RA) will also aim to observe at least one activity observed by each Gram Vikas data collector for each of the three meeting intervention activities.

The Gram Vikas mobilizers will also be trained by the Emory research team on two documentation tools: a record book and household visit behavior surveys. Mobilizers will track participant attendance at each activity they deliver, as well as other activity details, in a record book and will also fill out a brief behavior survey with caregivers at each household visit to track aspects of hardware use and behavioral adoption.

Following completion of the intervention, IDIs will be conducted with Gram Vikas mobilizers and caregivers who participated in the activities. A trained Emory RA will interview each Gram Vikas mobilizer to understand their experience with implementing the activities, what went well, what did not go well, and recommendations for the future. In a similar fashion, a team of trained RAs will conduct the IDIs with caregivers to capture their experience and feedback on the intervention activities.

### Data management

The baseline, endline and process evaluation surveys will be programmed for mobile data collection using the open source software Open Data Kit (ODK) [46]. Programmed skip patterns, numeric constraints for integer answers, and required response (with a ‘refusal’ response option) will ensure data quality and prevent missing data. The surveys will be administered using the ODK Collect application on an encrypted and password-protected Android phone. Completed surveys will be uploaded to a password-protected server that compiles the data. When ready for analysis, data will be downloaded from the server and saved to a password-protected cloud-based folder. Some research activities, such as the environmental sampling, will involve data collection using paper and pen. The data will be entered into an Excel database and the paper surveys scanned to create a digital copy, with all files saved in the secure cloud-based study folders.

IDIs will be audio-recorded upon participant consent. Recordings will be transcribed directly into English and the transcripts de-identified to ensure confidentiality. The audio-recordings and transcripts will be saved in the secure cloud-based study folders.

Only members of the research team will have access to the secure cloud-based study folders.

### Data analysis

#### Trial

We will employ an intention-to-treat analysis for all primary comparisons between the intervention and control arms. The effect of the intervention on JMP defined safe disposal will be assessed using a log-binomial model, which will yield the prevalence ratio of post-intervention safe disposal among intervention households relative to control households. We will use generalized estimating equations (GEE) with robust standard errors to account for village-level clustering and will adjust for stratified randomization by geo-demo group and baseline prevalence of safe disposal. If any relevant variables are found to be substantially imbalanced between the two arms at baseline then an additional model will adjust for these variables. All adjusted and unadjusted models will be reported. GEE will also be used to examine the impact of the intervention on secondary outcomes using the appropriate distribution and link function for each specific secondary outcome. If there is variation in the level of household participation in intervention activities, then a per-protocol analysis will be conducted to better measure the efficacy of the intervention on safe disposal behavior change under ideal conditions. A sensitivity analysis will also be conducted to examine differences in safe disposal between those households that were surveyed at baseline and endline compared to those only surveyed at endline. Lastly, we will employ mediation analysis [47] to examine which behavioral factors the CFM intervention influenced and which behavioral factors were then linked to changes in safe CFM behaviors, including safe disposal and child latrine training.

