### Study setting and population

The study will take place in Ganjam and Gajapati districts, an area in which the implementing partner Gram Vikas works and where a previous matched-cohort evaluation found low reports of safe disposal [13]. Both districts are predominantly rural (78% in Ganjam, 88% in Gajapati) with agriculture as the main occupation [24]. However, the districts differ in both their geography and demography. Ganjam district includes a varied geography of hills, valleys, coastal plains, and tableland where the vast majority of the population is Hindu (98.8%), only 3.4% belong to the Scheduled Tribe caste category, and 58.7% of rural women are literate [13, 24]. In contrast, Gajapati district is mostly hilly with a population that is 61% Hindu and 38% Christian, the majority (54.3%) are Scheduled Tribe, and 42.1% of rural women are literate [13, 24].

We specifically engaged rural villages that previously participated in Gram Vikas’s community-based water and sanitation program known as MANTRA (Movement and Action Network for Transformation of Rural Areas) [25]. In the MANTRA program the community is mobilized to construct latrines for each household (twin-pit pour flush latrines with attached bathing room) and once this is accomplished then Gram Vikas constructs a community water tank that provides piped water to all households. A sub-study from the matched cohort evaluation examined the CFM practices of caregivers of children < 5 years residing in MANTRA villages and who had access to improved sanitation [26]. The study found that 40.7% of caregivers reported safely disposing of their child’s feces into the latrine the last time the child defecated, with the majority of this safe disposal (84.7%) being a result of the child directly using the latrine. This is in contrast to the overall State of Odisha where only 13% of households practice safe disposal [13].

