## Village selection and random allocation

We randomly selected 74 villages from a sample frame of 501 MANTRA villages in Ganjam and Gajapati districts. Following baseline data collection, author [name] used stratified randomization to allocate villages into intervention or control arm on a 1:1 basis (Fig. 1). A computer-based random number generator was used to complete the allocation. Villages were categorized into one of five distinct geographic-demographic (‘geo-demo’) groups, which served as the stratification variable to ensure balance on a wide range of factors. Villages in each ‘geo-demo’ group have a distinct set of characteristics with regard to their geography (coastal, hilly, tableland, etc.), predominant religion and caste, village size, market access and other characteristics. The ‘geo-demo’ groups mostly align with the ‘block’ level administrative unit (a district subdivision), with several blocks falling under each group. As such, three of the ‘geo-demo’ groups are located entirely in Ganjam district while the remaining two are in Gajapati district. We used replacement re-randomization to ensure balance on two a priori specified variables: number of eligible households per village and village-level baseline reported safe disposal of child feces. We used the Mann-Whitney U Test to test if the distribution of villages on these two variables was not significantly different between the study arms. We also used an independent samples t-test to test if the mean baseline reported safe disposal of child feces was not significantly different between the study arms. The a priori balance criteria were met with the first randomization attempt. Participants and study investigators will not be blinded to village treatment assignment.

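### Covariates beyond stratum and baseline prevalence enter only through an undefined imbalance trigger, so child age, a likely strong predictor, is not fixed in the main model

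*Protocol article*

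**What the plan says.** Data analysis, Trial, describes a log-binomial GEE model with robust standard errors, clustered by village, which "will adjust for stratified randomization by geo-demo group and baseline prevalence of safe disposal". It then adds a conditional rule: if any relevant variables are "found to be substantially imbalanced between the two arms at baseline then an additional model will adjust for these variables". Neither what counts as relevant nor what counts as substantial is defined, and no candidate variables are listed. The paragraph goes on: "All adjusted and unadjusted models will be reported". It does not say in words which of these models carries the conclusion.

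Village selection and random allocation names two variables for the balance check, "number of eligible households per village and village-level baseline reported safe disposal of child feces", and reports: "The a priori balance criteria were met with the first randomization attempt".

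Study setting and population gives 40.7% safe disposal in comparable villages, "with the majority of this safe disposal (84.7%) being a result of the child directly using the latrine". The intervention section assigns hardware by age: basin and bucket below 7 months, training mat from 7 to below 48 months. Inclusion/exclusion criteria define baseline eligibility by age under 5 at the survey, and endline eligibility by age under 5 at intervention delivery.

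**The concern.** In a randomised trial any baseline imbalance is due to chance. Its size says nothing about whether a variable predicts the outcome, and prediction is what makes adjustment worth having. A rule keyed to imbalance can admit a useless covariate and pass over a useful one. With no threshold or candidate list, the content of the extra model is settled after someone has looked at the data.

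The trigger also reads the wrong sample for child-level variables. Baseline and endline are separate cross-sections with different age windows, and field work paused for six months between them. Balance in age at baseline is an imperfect guide to balance among the children analysed.

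The variable most plainly affected is child age. Whether a child uses the latrine unaided must depend on age to some degree, and that route makes up most of the outcome. Precision is at stake: the protocol reports that unequal cluster sizes already moved the detectable difference from 15 to 16 points. Clarity is a lesser stake, since up to three prevalence ratios will appear with none named as decisive.

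**Working it through.** **1. The plan's own figure.** Inputs from Sample size, Trial: 40.7% against 55.7%, ICC 0.103, 9 households per village, 10% loss, 80% power, alpha 0.05 (two-sided assumed).

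- Households per arm before clustering, unpooled variance: (1.960 + 0.842)² × (0.407×0.593 + 0.557×0.443) / 0.15² = 170.3.
- Cluster size after loss: 9 × 0.9 = 8.1. Design effect: 1 + 7.1 × 0.103 = 1.7313.
- Villages per arm: 170.3 × 1.7313 / 8.1 = 36.4, rounded up to 37. Pooled variance gives 37.2, so 38.
- Prevalence ratio: 0.557 / 0.407 = 1.37.

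The stated 37 reproduces. With an assumed cluster-size CV of 0.5 to 0.6 the detectable difference is 15.9 to 16.2 points, in line with the stated 16. The covariate point does not touch these figures.

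**2. How much of the outcome is the child's own latrine use.** 0.407 × 0.847 = 0.345, or about 34.5 of 40.7 points. The remaining 6.2 points are caregiver disposal. This makes a strong link with age plausible; it does not measure it.

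**3. Overlap of the two samples.** At least six months separate baseline from delivery. If ages were uniform over 60 months (an assumption), at least 6/60 = 10% of the children eligible at baseline would be too old by delivery, with newborns entering. Most children overlap, but not all.

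**4. What age adjustment could gain.** The age slope is an assumption, shown over a range. Common assumptions: 74 villages, mean size about 8, ages uniform from 0 to 5 years, true prevalences 40.7% and 55.7%, log-link Poisson GEE with robust standard errors.

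First, arm alone against arm plus age (300 runs per slope, village SD 0.62 on the logit scale, Monte Carlo error about 2 points on power):

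| Age slope (log-odds per year) | SD of log PR, without age | with age | Change | Power without / with | Mean PR without / with |
|---|---|---|---|---|---|
| 0 | 0.1171 | 0.1178 | about 0 | 80% / 81% | 1.37 / 1.37 |
| 0.5 | 0.1085 | 0.1055 | −3% | 82% / 86% | 1.37 / 1.37 |
| 1.0 | 0.1020 | 0.0905 | −11% | 87% / 94% | 1.36 / 1.37 |

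Type I error without age was 5% to 7%.

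Second, the comparison that matters: the planned covariates (stratum and baseline prevalence) against the same plus age bands. The SD of the log prevalence ratio fell by 0%, 4% and 16% at slopes of 0, 0.5 and 1.0, with no material change in the ratio. A repeat with 800 runs per slope and different assumed variation (between-stratum SD 0.3, village SD within stratum 0.54) gave 0%, 3% and 9%. The 16% is therefore an upper end.

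**5. In terms of detectable difference.** The 16-point effect is a ratio of 0.567 / 0.407 = 1.393, with log 0.3315. If a 4% cut carried over: exp(0.3315 × 0.96) × 40.7% = 55.9%, or 15.3 points. With a 16% cut: exp(0.3315 × 0.84) × 40.7% = 53.8%, or 13.1 points.

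**The case against.** The strongest reply is that the main model's covariates are fixed in advance and the trigger feeds only an additional model. A reader might infer that the primary analysis itself is chosen by imbalance; the text does not support that. A reader might also infer room for selective reporting. The commitment to report every model limits this, and the stratum-plus-baseline model is the natural reading of the lead analysis. What remains is that the protocol does not say so, and full reporting does not settle which estimate decides if they differ.

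Second, the absence of age could be filled by an analysis plan that is not shown, and adjustment for precision is optional. That stands for the absence taken alone. It does not excuse the trigger, which this document itself sets and which decides how age would enter.

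Third, no passage gives safe disposal by age. Calling age the main driver of the outcome goes beyond the documents: the 84.7% describes the route of disposal, not an age gradient. Any single figure for lost power rests on an assumed slope, so only a range is defensible.

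Fourth, one of the two balance-check variables, eligible households per village, is not in the model. A reader might see a mismatch between randomisation and analysis that undermines the test. It matters little: no draw was rejected, and both the stratifier and the balance variable tied to the outcome are adjusted for. Omission would at most tend to be conservative.

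**Conclusion.** The concern holds in limited form. The protocol fixes a poor rule for further covariates: it selects on undefined chance imbalance, in a sample that only partly overlaps the one analysed, and confines what it selects to an additional model. Child age, a likely strong predictor that is needed for eligibility, is not a fixed covariate.

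The cost is precision. In the simulations the prevalence ratio stayed at about 1.37 whether or not age was included, so nothing here supports a claim of bias or of an invalid test. The gain forgone runs from none to about a 16% smaller standard error of the log prevalence ratio. It depends on an age slope the documents do not give, and the top of the range needs a steep one (1.0 log-odds per year). This should be changed before endline, but the trial's validity does not turn on it.

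**What to change.** Before endline data are seen, state one confirmatory model: the GEE prevalence ratio for arm, adjusted for geo-demo group, village baseline prevalence of safe disposal, and child age in bands or as a spline, whatever the observed balance. Number of eligible households per village may be added for consistency with the balance check, with little practical effect expected. Name a log-link Poisson GEE with robust standard errors as the fallback if the log-binomial model does not converge, which becomes more likely with age included. Label the unadjusted model supportive. Drop the imbalance-triggered model or label it exploratory.

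The cost is analysis wording only. Age must be established to confirm eligibility, so it should already be available, and the intervention cannot alter it. The sample size stays as it is.

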**Methods:**

The intervention consists of six behavior change strategies together with hardware provision: wash basin and bucket with lid to aid safe management of soiled nappies and a novel latrine training mat to aid safe disposal and latrine training. The intervention will be offered at the village level to interested caregivers of children < 5 years of age by a community-based organization. Following a baseline survey, 74 villages were randomly allocated to either intervention or control arm. The primary outcome is caregiver reported safe disposal of child feces after last defecation, either by the caregiver disposing of the child’s feces into the latrine or the child using the latrine, measured approximately four to six months following intervention delivery. Secondary outcomes include fecal contamination of household drinking water and the childs’ hands. A process evaluation will also be conducted to assess intervention fidelity and reach, and explore implementer and participant feedback.

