#### Process evaluation

Surveys will be completed in a subset of intervention villages, dependent upon resources and travel logistics, to document fidelity and reach for each type of intervention activity delivered. In-depth interviews (IDIs) will be conducted with both Gram Vikas mobilizers and participants to capture their perspective and feedback on the intervention, as well as contextual factors that impacted delivery. Approximately 30 caregivers and each Gram Vikas mobilizer will be interviewed. More or fewer participants may be interviewed depending on saturation of findings. The caregivers will be purposively selected based on certain characteristics, such as their child’s age, in order to capture a range of perspectives. To act as a check on delivery and as another measure of reach, the endline trial survey will include questions for intervention households about participation in the activities. To assess spillover, control households will be asked questions about whether or not any activities related to CFM took place in their village and if they have ever heard of or seen a latrine training mat.

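### The per-protocol analysis is presented as a better measure of efficacy, but participation is voluntary, follows randomisation and is recorded in one arm only, so a conventional per-protocol contrast is not randomised

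*Protocol article*

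**What the plan says.** Under Data analysis, Trial, the primary rule is clear: "We will employ an intention-to-treat analysis for all primary comparisons between the intervention and control arms". The same paragraph adds a conditional analysis. It begins "If there is variation in the level of household participation in intervention activities", and continues: "then a per-protocol analysis will be conducted to better measure the efficacy of the intervention on safe disposal behavior change under ideal conditions". The article does not define the per-protocol set, an attendance threshold or the comparator, and does not say whether the covariates of the main model carry over.

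Three other places determine what such an analysis can be:

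- **Who takes part.** The Methods paragraph of the Abstract says: "The intervention will be offered at the village level to interested caregivers".
- **Where participation is recorded.** Under Data and sample collection, Process evaluation: "Mobilizers will track participant attendance at each activity they deliver". Under Sample size, Process evaluation: "the endline trial survey will include questions for intervention households about participation in the activities".
- **What controls are asked.** The same Sample size subsection says that "control households will be asked questions about whether or not any activities related to CFM took place in their village", together with whether they know of the training mat. These are spillover questions. They do not show who would have attended had the programme been offered.

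**The concern.** Attendance is a choice made after allocation, and it is seen in one arm only. Control villages contain caregivers who would have attended and caregivers who would not, and the planned data do not tell them apart. Restricting the intervention arm to attenders while leaving the control arm unrestricted would compare a selected group with an unselected one. Any difference in what attenders would have done without the programme then enters the estimate as if it were an effect.

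This is more than a missing definition. The article assigns the analysis a property, that of measuring efficacy better, which a conventional per-protocol contrast lacks in this design. The Discussion links the results to wider programming and government campaigns. If low attendance dilutes the intention-to-treat result, a figure described as the better measure of efficacy is the one most likely to be quoted.

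**Working it through.** **The plan's own figure.** The article gives no number for the per-protocol analysis. The only related figure is the 37 villages per arm for the primary comparison. With 40.7% against 55.7%, two-sided 5% (sidedness assumed), 80% power and unpooled variance:

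- n = (1.960 + 0.842)^2 x (0.407 x 0.593 + 0.557 x 0.443) / 0.15^2 = 170.3 per arm.
- Applying the 10% loss to cluster size, m = 9 x 0.9 = 8.1.
- Design effect = 1 + 7.1 x 0.103 = 1.731.
- Villages = 170.3 x 1.731 / 8.1 = 36.4, so 37. The ratio 0.557 / 0.407 = 1.37 also agrees.

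The primary design figure reproduces and is not in question here.

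**Selection bias of participants against all controls.** Inputs: control prevalence p = 0.407 (Sample size, Trial); participation share f and untreated difference delta (participants minus non-participants), both assumed because the document gives neither.

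The overall untreated prevalence is p = f x pP + (1 - f) x pN, with pP - pN = delta. Hence pP = p + (1 - f) x delta. With no true effect and no adjustment, the contrast shows (1 - f) x delta in place of zero, and the ratio is pP / p.

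| f | delta (points) | Bias (points) | pP | Ratio with no effect |
|---|---|---|---|---|
| 0.85 | +5 | +0.75 | 0.4145 | 1.02 |
| 0.70 | +10 | +3.0 | 0.437 | 1.07 |
| 0.50 | +20 | +10.0 | 0.507 | 1.25 |
| 0.70 | 0 | 0 | 0.407 | 1.00 |
| 0.70 | -10 | -3.0 | 0.377 | 0.93 |

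Against the 15-point target, the second row is one fifth and the third row two thirds.

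**Chance of a false significant result.** This uses delta = +20 points, 37 villages per arm, m = 8.1 for controls and 8.1 x f for participants, and ICC 0.103:

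- f = 0.7: effective sizes 173.1 and 141.7, standard error 0.056, bias 0.06, rejection probability about 19%.
- f = 0.5: effective sizes 173.1 and 114.0, standard error 0.060, bias 0.10, rejection probability about 39%.

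The nominal level is 5%.

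**With a real effect.** Suppose the intention-to-treat effect is +15 points and acts only through participation, with f = 0.7. The effect in participants is 0.15 / 0.7 = 21.4 points. The participants-against-controls contrast would show 21.4 + 0.3 x 10 = 24.4 points for delta = +10, and 21.4 - 3.0 = 18.4 for delta = -10.

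**Would the stated covariates remove the bias?** The main model adjusts for geo-demo group and baseline prevalence of safe disposal. Prevalence reads as a village quantity, which is how Village selection and random allocation uses it. The surveys are described as cross-sectional, and some households are expected only at endline. Village covariates cannot remove selection between households in the same village.

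**The case against.** A reader might infer that the protocol sets attenders against all controls, that the result will be too high, and that no per-protocol analysis could estimate efficacy. The document does not support any of these as stated.

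- **Comparator.** It is not named. All controls is the likely choice given what is recorded, but a fuller protocol or an analysis plan may define the set and the handling of selection. That lack of detail is not the fault here.
- **Feasibility of adjustment.** Psychosocial factors and social support are measured at baseline in both arms (Study outcomes and measures). For households surveyed then, adjustment or weighting for predictors of attendance is possible.
- **Direction.** Motivated caregivers may well have better untreated practice, but the article also gives reasons for the reverse. Hardware is listed only for children under 48 months although eligibility runs to under 5 years. In the earlier sub-study, 84.7% of safe disposal was the child using the latrine. Families whose child already does so may have less reason to attend.
- **The alternative has its own weakness.** A complier-average effect assumes that assignment does nothing for non-attenders. Norm techniques, household support and village stakeholders may reach them. A high attendance threshold makes this worse, because hardware is handed out at the opening meeting and those below the threshold may already be treated.
- **Consequence.** The analysis is conditional and supplementary; intention-to-treat governs the primary comparisons.

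All five points stand as limits. None restores the stated property: a contrast with unknown selection bias does not measure efficacy better.

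**Conclusion.** The concern holds as a fault in the claim made for the analysis. Because attendance is voluntary, follows randomisation and is seen in one arm, a conventional per-protocol contrast is non-randomised, with bias of unknown, plausibly upward, direction. Under assumed inputs the no-effect prevalence ratio in the cases worked ranges from 0.93 to 1.25, and it is 1.00 if attenders and non-attenders have the same untreated practice. These figures assume an unadjusted comparison with all controls; the participation shares and selection differences are illustrations, not document values. The primary intention-to-treat conclusion and the sample size are unaffected. This should be corrected, but it does not threaten the trial's main result.

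**What to change.** 1. Delete the statement that the per-protocol analysis measures efficacy better. Label any as-participated contrast supportive and non-randomised.
2. Make the main participation-adjusted estimate a complier-average effect, with randomised village arm as the instrument. Define participation in advance as any attendance, including the opening meeting. Use geo-demo group and village baseline prevalence as covariates, with village-clustered standard errors. No delivery to control villages is planned, so non-compliance should be essentially one-sided.
3. State the exclusion restriction and its main threat. If non-attenders gain s points through spillover within the village, the intention-to-treat effect is f x tau + (1 - f) x s, where tau is the effect in attenders. Dividing by f gives tau + s x (1 - f) / f. At f = 0.7 that inflates the estimate by 0.43 points for each point of spillover; at f = 0.5, by one point.
4. The estimate arises as a difference in proportions. To match the planned scale, a complier prevalence ratio can be formed as attenders' endline prevalence divided by that prevalence minus the complier effect.

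The cost is a change of wording and one additional model on attendance data already planned. The interval will be wider than a per-protocol interval, and the estimate rests on an assumption that must be stated. The primary analysis does not change.
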